#### Psychosocial Health Questionnaires

To gather information about the demographic profile and SES, health behaviors, and psychosocial health indicators of each participant, the following assessments will be completed by each participant by means of a questionnaire survey:

Demographic data and SES determined through household income and assets (property and car ownership).Cigarette smoking, alcohol use, and screen time per day.Subjective perceived health measured with 2 items from the 12-item short form health survey, adapted from the SF-36 [51]. Participants will be asked to rate the following questions: *In general, would you say your health is?* and *How motivated are you to improve your lifestyle?*Work-related stress will be assessed using the short version of the original Effort-Reward Imbalance questionnaire [52].The Shirom-Melamed Burnout Measure, a validated and widely used tool, will be used to assess occupational burnout [53].Diet and nutritional analysis with a 24-hour dietary recall.The General Health Questionnaire will assess mental distress or minor psychiatric morbidities [54].Subjective sleep complaints will be assessed utilizing the brief 7-item self-report Insomnia Severity Index [55].

#### Data Collection and Statistical Analysis

The following data will be collected: (1) quantitative data on blood pressure, glycated hemoglobin and blood lipids, anthropometry and levels of physical fitness, cognitive performance and psychosocial health, (2) SES and demographic data, and (3) qualitative data on the feasibility and acceptability of the intervention measures implemented through FGDs. Quantitative data will be entered twice and cross-checked using EpiData version 3.1 (EpiData Association; Odense, Denmark). Cleaned data will be transferred to STATA version 13.0 (STATA Corp, College Station, TX, United States of America). Questionnaire data will be collected using the software package EvaSys (Survey Automation Suite, version 7.1) and analyzed with STATA.

Clinical and anthropometric indicators, physical fitness, cognitive performance, and psychosocial health values will be summarized by their mean and SD at normal distribution and otherwise by their median and interquartile ranges. Questionnaire information on psychosocial health will be expressed as a percentage.

For the analysis of cross-sectional and longitudinal associations, mixed linear or mixed logistic regression models will be used, depending on the type of outcome variable. These models will be adjusted for clustering within classes and schools using random intercepts. In analyses of cross-sectional associations, the models will include personal characteristics of children, such as gender and age, SES of parents or guardians, and other potential confounders of the associations of interest. Models assessing intervention effects will additionally include 3 indicator variables, as defined at the level of schools, 1 for schools of the intervention arm, 1 for schools receiving teacher workshops, and 1 for schools receiving teacher coaching. In addition, these models may include the value of the respective outcome variable at baseline. As intervention effects may also depend on the child’s initial characteristics, stratified analyses and analyses with interaction terms will be performed. Potential effect modifiers to be tested include gender, age, SES, ethnicity, health status, and physical fitness at baseline.

The primary objectives of the statistical analyses are (1) to assess the physical fitness of the participants and their associations with cognitive performance and psychosocial health at the beginning and over the course of the intervention, and (2) the effect of interventions on disease status and other health parameters. The secondary objective is to assess the feasibility and acceptability of the health interventions, as determined by FGDs.

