### Study Design

The intervention arm targeting school children is designed as a 36-week RCT, including an intervention group (4 schools) and a control group (4 schools). The 4 intervention schools, assigned through randomization, will be further allocated randomly to the following intervention conditions: all schools will receive the teaching materials (*KaziKidz* and *KaziHealth*), but the components workshop and coaching will be assigned as follows: (1) teaching materials only, (2) teaching materials plus workshops, (3) teaching materials plus coaching, and (4) teaching materials plus workshops plus coaching (Figure 3).

The 4 remaining schools will be assigned to the control group. In the control schools, there will be documentation of routine PE and sports in school.

The primary comparison will be made between the 4 intervention schools and the 4 control schools to assess the benefit of teaching materials. Secondary comparisons will be between teaching materials plus coaching and teaching materials without coaching or teaching materials plus workshop and teaching materials without workshop. In view of the factorial design of our study, each comparison group consists of 2 schools.

By focusing on change in quantitative outcomes from baseline to follow-up, preexisting differences between schools should play less of a role. Although the intervention covers grades 1 to 7, in each school, 1 class each from grades 4, 5, and 6 will be randomly selected for evaluation of the intervention. After completion of the baseline assessment, children of the intervention schools will take part in a school-based health promotion program (32 school weeks, 1 PE lesson of 40 min per week, 1 moving-to-music lesson of 40 min per week, 3 health education lessons, and 3 nutrition education lessons of 40 min per year across the whole study period). The follow-up will be after 36 weeks (Figure 4). Qualitative data on the feasibility and acceptability of the intervention measures will also be collected from teachers through focus group discussions (FGDs).

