### Study Participants

The effect of the *KaziKidz* teaching material will be evaluated in 1 randomly selected class in grades 4, 5, and 6 (=intermediate phase) in each of the 8 study schools (interventions are randomly assigned to any of the 4 northern area or 4 township schools) even though *KaziKidz* teaching material will be offered to all classes in grades 1 to 7 as part of the life skills and life orientation courses in the school curriculum.

For *KaziHealth*, all teachers from the 8 schools will be invited to participate in the program. All participating teachers will undergo the full health risk assessment, and teachers at the intervention schools will have the option to participate in the 20-week intervention. The teachers from the control schools will be offered the intervention program after the completion of the study.

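### Grade is a fixed design factor in every school but is not named in the children's models; naming it costs almost nothing and protects the standard error of the arm contrast if change differs by grade

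*Protocol article*

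**What the plan says.** **Sampling.** The Study Design section of the protocol article states that "in each school, 1 class each from grades 4, 5, and 6 will be randomly selected for evaluation of the intervention". Study Participants repeats it: the teaching material is "evaluated in 1 randomly selected class in grades 4, 5, and 6 (=intermediate phase) in each of the 8 study schools". This gives 8 × 3 = 24 classes, with grade fully crossed with school and the same in both arms.

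**Random effects.** Data Collection and Statistical Analysis says: "These models will be adjusted for clustering within classes and schools using random intercepts".

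**Covariates.** For cross-sectional associations, "the models will include personal characteristics of children, such as gender and age, SES of parents or guardians", and the sentence goes on to admit further potential confounders. The list is open, and grade is not on it.

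**Intervention models.** "Models assessing intervention effects will additionally include 3 indicator variables, as defined at the level of schools": one for the intervention arm, one for workshops and one for coaching. In addition, "these models may include the value of the respective outcome variable at baseline". Grade is not named here, nor among the candidate effect modifiers.

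**Where associations matter.** The first primary analysis objective is "to assess the physical fitness of the participants and their associations with cognitive performance and psychosocial health". Cognitive performance is taken from the sum of four school exam subjects.

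**The concern.** A random class intercept treats the classes within a school as exchangeable. Here they are one grade 4, one grade 5 and one grade 6 class, repeated identically in every school. A systematic difference between grades is therefore a fixed effect of the design. With no grade term it is counted as random class variation.

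Two things could follow. First, grade adds nothing to the true variance of the arm contrast, but an inflated class variance can enter its estimated standard error, which matters with only 4 schools per arm. Second, if fitness and exam marks both shift with grade, part of that shared shift could appear as an association between them.

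Age is a partial substitute at best. With class intercepts in the model, the age slope is set largely by age differences within a class, so it takes out only part of a step between grades.

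**Working it through.** **1. The protocol's own power.** Inputs from Sample Size and Randomization: effect 0.5σ, intraclass correlation 0.04, 100 children per school, 400 per arm, 5% level (two-sided assumed).
- Design effect = 1 + 99 × 0.04 = 4.96. Effective n per arm = 400/4.96 = 80.6.
- SE = √(2/80.6) = 0.1575σ. Power = Φ(0.5/0.1575 − 1.96) = Φ(1.215) = 88.8%.

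The stated figure of over 85% is reproduced. A t reference on 6 df gives 75.4%; that is a separate matter.

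**2. How grade reaches the standard error.** Assume grade effects −g, 0, +g on the change outcome, 33 children per class, school variance 0.04, residual variance 0.96 and no other class variance.
- True variance of a school mean = 0.04 + 0.96/99 = 0.0497. The SE of the 4-versus-4 contrast is √(0.0497/2) = 0.158. It does not depend on g, because each school mean averages the same three grades. In simulation the SD of the estimate was 0.157 to 0.158 at every g.
- Without a grade term, the estimated class variance rises by (g² + 0 + g²)/2 = g². Restricted maximum likelihood offsets this by lowering the school variance by g²/3, but not below zero.
- The offset is exhausted on average when g²/3 = 0.04, that is at g = 0.35.
- Past that point the school and class strata are pooled. At g = 0.5 the class stratum, on the school-mean scale, is (0.25 + 0.96/33)/3 = 0.0930. The pooled value is (6 × 0.0497 + 16 × 0.0930)/22 = 0.0812, so SE = √(0.0812/2) = 0.202. The simulated mean was 0.203.

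In simulation the school variance was set to zero in 3% of runs at g = 0, 17% at 0.2, 42% at 0.3 and 90% at 0.5. The mean SE was 0.151, 0.154, 0.162 and 0.203 respectively.

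**3. Power, without versus with grade as a fixed effect** (no age term):

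| Grade step g | Normal critical value | t, 6 df |
|---|---|---|
| 0.2σ | 86.9% vs 87.1% | 74.6% vs 75.0% |
| 0.3σ | 86.0% vs 87.2% | 72.8% vs 75.4% |
| 0.4σ | 82.0% vs 87.0% | 65.1% vs 75.2% |
| 0.5σ | 74.1% vs 87.1% | 51.6% vs 75.5% |

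At g = 0 power is the same with and without grade (75.4%, t on 6 df).

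**4. Sensitivity at g = 0.3σ.**
- Adding class variance 0.02: 81.2% vs 83.2% (normal) and 66.2% vs 69.9% (t).
- Also lowering school variance to 0.02: 91.8% vs 94.3% and 80.4% vs 86.3%.
- Average intervention-versus-control contrast in the three-indicator model, 4 school-level df, variances as in step 2: 60.9% vs 66.2% (t).

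**5. How much age removes.** Assume one year of age per grade and a within-class age SD of 0.8 years. At g = 0.3 the information on the age slope per class is 33 × 0.64/0.96 = 22.0 within classes and (2/3)/(0.09 + 0.96/33) = 5.6 between grades. With no age trend within grades, the fitted slope recovers about 5.6/27.6 = 20% of the grade step.

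**6. Fitness-marks association.** Simulation of 24 classes of 42 children, true slope zero, grade steps of 0.2 to 0.5 SD in both variables. With class and school intercepts and age, the absolute bias is about 0.003 to 0.021 SD per SD, against an SE of about 0.032 (0.021/0.032 = 0.66 SE). With 0.5 SD steps in both, the bias is 0.143 with no clustering terms, about 0.02 with intercepts and age, and about zero once grade is added.

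**The case against.** **The list is open.** The covariate sentence is introduced by an example phrase and admits other potential confounders, and a final list is commonly left to an analysis plan that is not shown. This stands for the association models: a reader might infer that grade is excluded from them, and the text does not say so. It helps less for the arm contrast. Grade is balanced over arms, hence not a confounder there, so a confounder clause would not bring it in.

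**The arm effect is not biased.** A reader might infer that grade confounds the intervention comparison. It cannot, because every school supplies the same three grades. The error is in the safe direction: with a t reference on 6 df and g = 0.5σ, the false-positive rate is 0.2% without grade and 4.5% with it.

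**Large losses need large grade effects.** A reader might infer that the trial loses power regardless, or that the stated power fails. Neither follows. A step of 0.5σ puts grades 4 and 6 a full σ apart in change over 36 weeks, twice the planned intervention effect. Nothing in the protocol supports a step of that size, and several outcomes are already standardised for age. This objection stands, and it limits the point to a conditional one.

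**The association leak is small.** A reader might infer that the fitness-marks result is materially confounded. The class intercept already removes most of the problem, so that reading is not supported.

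**Conclusion.** The point holds as a conditional, minor matter of model specification. The protocol fixes grade in the sampling but does not name it in the analysis. If change differs by grade, the standard error of the arm contrast can be too large, while the estimate stays unbiased.

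At the protocol's intraclass correlation of 0.04, with no further class variance, the loss is negligible up to a step of about 0.2σ per grade, about 1 to 3 points at 0.3σ and 5 to 10 points at 0.4σ. The lower end of each range uses a normal critical value and the upper end t on 6 df. Under the other settings tried at 0.3σ, the loss reaches about 5 to 6 points. Grade steps, class variance and age spread are all assumptions; the protocol gives none of them. The age term, if used, would reduce the losses only in part.

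For the fitness-marks association, the residual bias is up to about 0.02 SD per SD, under one standard error, and the plan as worded permits adjustment for grade.

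**What to change.** In Data Collection and Statistical Analysis, name grade (4, 5, 6) as a fixed effect with two indicators in all the children's mixed models, for intervention effects and for associations. Keep age as a covariate, and keep the class and school random intercepts.

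**Cost.** One clause of text and no new data, since the grade of every class is known. There are 8 × (3 − 1) = 16 class-within-school degrees of freedom. Grade uses 2 of them, leaving 14, and none at school level, because it is balanced over schools. If the grades do not differ, power is unchanged.

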### Sample Size and Randomization

Assuming that the prevalence of obesity varies across schools according to a log-normal distribution with a mean value of 3% and a SD of 2%, 125 children per school in each of the 8 schools would provide a prevalence estimate between 1.5% and 5% with a probability of 95%. Under this assumption, 95% of school-specific prevalence would range between 0.8% and 8.2%. Hence, our aim is to recruit 125 children per school.

The power calculation for the intervention study is based on the change in a quantitative outcome variable from baseline to follow-up. We denote the SD of its change across schools and children by sigma (σ). Assuming an intervention effect size of 0.5 x σ and an intraclass correlation of .04 for the clustering of individual changes within schools (corresponding to a random effect SD of 0.2 x σ), 400 children in the 4 intervention schools (ie, 100 children per school) participating in baseline and follow-up, and 400 children in the 4 control schools would provide over 85% power to observe a statistically significant difference in the mean change of the respective outcome variable between intervention and control schools at the 5% level.

Enrollment of schools will be done by the local research team. To prevent contamination of the intervention effects, schools rather than classes were randomized in January 2019. Before randomization, schools were divided into 2 geographic groups; namely, township areas and northern areas, each containing 4 schools. Township areas are predominantly inhabited by black Africans and northern areas by colored people (after an apartheid-era classification, which refers to people from a multiracial ethnic background and can include persons of Khoi and San origin).

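### The primary 4-versus-4 school comparison, its stated purpose, its power figure and the three-indicator model do not describe the same effect, and the article does not say which contrast is primary

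*Protocol article*

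**What the plan says.** Three statements in the protocol article bear on the primary analysis.

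- **Study Design** fixes the comparison and its purpose: "The primary comparison will be made between the 4 intervention schools and the 4 control schools to assess the benefit of teaching materials". The four intervention schools each receive a different scheme: "1) teaching materials only, (2) teaching materials plus workshops, (3) teaching materials plus coaching, and (4) teaching materials plus workshops plus coaching". The workshop and coaching comparisons are secondary: "In view of the factorial design of our study, each comparison group consists of 2 schools".
- **Sample Size and Randomization** powers the difference between intervention and control schools. "Assuming an intervention effect size of 0.5 x σ", an intraclass correlation of .04 and 100 children in each of 8 schools "would provide over 85% power to observe a statistically significant difference in the mean change of the respective outcome variable" at the 5% level.
- **Data Collection and Statistical Analysis** gives the model: "Models assessing intervention effects will additionally include 3 indicator variables, as defined at the level of schools, 1 for schools of the intervention arm". The other two indicators mark the added components and enter the same model: "1 for schools receiving teacher workshops, and 1 for schools receiving teacher coaching". On clustering: "These models will be adjusted for clustering within classes and schools using random intercepts".

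No other model is named for the primary comparison. The article does not say which coefficient, or which combination of coefficients, is the primary estimate.

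**The concern.** When workshop and coaching indicators stand in the same model as the intervention indicator, the intervention coefficient no longer averages over the four intervention schools. It becomes the effect where both components are absent, that is, of materials alone. This is a different quantity from the pooled difference that is declared primary and powered, and it is estimated less precisely.

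The pooled difference has the opposite problem. It mixes materials with workshops and coaching in three of the four intervention schools, so it cannot be called the benefit of the materials.

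Two analysts following the article could therefore report different primary effects from the same data. If workshops or coaching help, the coefficient is smaller than the package effect and is tested with less power, so a null result could be misread. If the pooled result is reported as the effect of the materials, it is misattributed.

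**Working it through.** **Inputs.** From Sample Size and Randomization: effect 0.5σ, intraclass correlation 0.04, 100 children per school, 4 schools per arm, 5% level. Two-sided testing is assumed, since sidedness is not stated. From Study Design: one school per scheme. With I = intervention, W = workshops and C = coaching, the intervention schools are (I, W, C) = (1,0,0), (1,1,0), (1,0,1), (1,1,1), and the four controls are (0,0,0).

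**1. Reproduce the plan's power.**
- Variance of a school mean change: 0.04 + 0.96/100 = 0.0496σ².
- Pooled contrast: variance 0.0496 × (1/4 + 1/4) = 0.0248σ², SE = 0.157σ.
- Normal approximation: Φ(0.5/0.1575 − 1.96) = Φ(1.215) = 88.8%.

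This agrees with the stated figure of over 85%, so that figure fits the pooled contrast with a normal reference.

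**2. What the intervention coefficient estimates.** Least squares on the eight school means with columns 1, I, W, C gives the coefficient b_I these weights:

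| School(s) | b_I | Pooled contrast |
|---|---|---|
| Each control | −1/4 | −1/4 |
| Materials only | +3/4 | +1/4 |
| Materials + workshops | +1/4 | +1/4 |
| Materials + coaching | +1/4 | +1/4 |
| Materials + both | −1/4 | +1/4 |

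Under additivity, the pooled difference = b_I + ½b_W + ½b_C. The two agree only if (b_W + b_C)/2 = 0. As an illustration with assumed effects of 0.5σ (materials), 0.1σ (workshops) and 0.2σ (coaching), b_I targets 0.50σ and the pooled contrast targets 0.5 + 0.05 + 0.10 = 0.65σ. A simulation of 50,000 sets of school means gave 0.50 and 0.65.

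**3. Precision.** In units of the school-mean variance:
- b_I: 4 × (1/16) + (9 + 1 + 1 + 1)/16 = 0.25 + 0.75 = 1.00, so SE = √0.0496 = 0.223σ.
- Pooled contrast: 8 × (1/16) = 0.50, so SE = 0.157σ.

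The variance ratio is exactly 2. Adding a term for area, the randomization stratum, leaves both multipliers unchanged.

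**4. Power at 0.5σ.**

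| Estimate | Normal | t, school-level df |
|---|---|---|
| Pooled, single indicator | 88.8% | 75.4% (6 df) |
| b_I, three indicators | Φ(0.5/0.2227 − 1.96) = 61.2% | 40.4% (4 df) |
| b_I + ½b_W + ½b_C, three indicators | 88.8% | 66.6% (4 df) |

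The last row is the pooled contrast recovered from the article's own model: the same estimate and variance, with two fewer degrees of freedom.

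**The case against.** The strongest reply has four parts.

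- **The model contains the primary contrast.** A reader might infer that the three-indicator model cannot estimate the 4-versus-4 comparison. That is not so: b_I + ½b_W + ½b_C recovers it exactly with no variance penalty. The article also never says that b_I is the primary test. This part stands. The fault is in the unstated contrast, not in what the model can do.
- **b_I fits the stated purpose.** If the aim is the benefit of the teaching materials, b_I estimates it under additivity, using all eight schools. This also stands, but the over-85% power then belongs to a different quantity. Elsewhere the Objectives and Rationale speak of the effect of an intervention package, which favours the pooled contrast.
- **An analysis plan could name the contrast.** That is reasonable for a condensed article, and silence alone would be no finding. Here, however, the comparison, purpose, power and model are all stated, and no reading makes them agree.
- **The size can be exaggerated.** Setting 40% against the stated 85% mixes a t-based figure with a normal-based one. Part of the t-based shortfall comes from having only eight schools, which is a separate matter. Likewise, a reader might say that three quarters of the intervention weight rests on one school. That is a net figure; in absolute weight it is 0.75 of 1.50, or half.

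**Conclusion.** The inconsistency holds, in a limited form. If the target is the pooled comparison, the power figure fits, but the intervention coefficient is not the estimate and the purpose clause misattributes the result. If the target is the materials alone, the coefficient fits under additivity, but the power claim does not.

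The loss applies only if the intervention coefficient is taken as the primary result. Like for like, power at 0.5σ then falls from 88.8% to 61.2% (normal) or from 75.4% to 40.4% (t, 6 against 4 df). The documents do not support saying that the trial as planned has 40% power, or that its model cannot answer the primary question.

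The figures assume equal school sizes, two-sided testing and the article's own intraclass correlation. Class-level clustering is not quantified; in a balanced layout it would scale both variances alike and leave the ratio at 2. With eight schools, which contrast is reported could decide the conclusion, so this should be settled before the follow-up data are analysed.

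**What to change.** 1. Define the primary estimand as the average effect of the intervention package over the four schemes, and reword the purpose clause in Study Design to match.
2. Prespecify one way to estimate it:
   - a single intervention indicator plus area; or
   - the existing three-indicator model with workshops and coaching each coded +½ or −½ within the intervention arm and 0 in controls. The intervention coefficient then has weights of 1/4 per school and variance 0.50. This is the same as reporting b_I + ½b_W + ½b_C under 0/1 coding.
3. Report the materials-only effect as a separate secondary estimate with its own interval, stating that it rests on additivity and is not covered by the over-85% power claim.

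**Cost.** Only coding and wording change; no new data are needed. The primary result can no longer be described as the effect of the materials alone. Keeping the component terms costs two school-level degrees of freedom (66.6% against 75.4% power with t, before any area term). Dropping them moves any real workshop or coaching effect into the variation between intervention schools. Either choice is defensible if made in advance. Neither cures the small number of schools: the single indicator plus area, on 5 df, has about 72% power with t.

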The randomization into intervention and control schools was done separately in each of the 2 groups so that each group was assigned 2 intervention and 2 control schools. To keep the design as balanced as possible, the 4 intervention schemes (ie, teaching materials only, teaching materials plus teacher workshops, teaching materials plus teacher coaching, and teaching materials plus teacher workshops plus teacher coaching) will be assigned in such a way that the intervention schools of 1 group will get teaching materials plus either teacher workshops or teacher coaching. Randomization will allow to determine which of the 2 groups gets which of the 2 pairs of intervention schemes. Sequentially numbered, opaque, sealed envelopes will be used for the assignment of the intervention arms to the schools.

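### Schools were randomised within township and northern areas, but the listed intervention-model terms omit area: effects stay unbiased, while power is lost if the areas differ in change

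*Protocol article*

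**What the plan says.** Under Sample Size and Randomization the protocol article states: "Before randomization, schools were divided into 2 geographic groups; namely, township areas and northern areas, each containing 4 schools". On the draw itself it says: "The randomization into intervention and control schools was done separately in each of the 2 groups". The split was even, with two schools per arm in either area. The additional components were also arranged by area: "the intervention schools of 1 group will get teaching materials plus either teacher workshops or teacher coaching". By elimination, the two intervention schools of the other area get materials only and materials plus both components.

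Under Data Collection and Statistical Analysis: "These models will be adjusted for clustering within classes and schools using random intercepts". For the intervention models: "Models assessing intervention effects will additionally include 3 indicator variables, as defined at the level of schools". The three are intervention arm, workshops and coaching; the baseline value of the outcome is optional. Area is not named. Its nearest proxy is ethnicity, since "Township areas are predominantly inhabited by black Africans and northern areas by colored people", but ethnicity enters only here: "Potential effect modifiers to be tested include gender, age, SES, ethnicity, health status, and physical fitness at baseline".

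**The concern.** Area was used to restrict the randomisation, and it is missing from the school-level terms of the model meant to analyse that randomisation. With 2 and 2 schools per area, a difference between areas in mean change cancels out of the treatment contrast and adds nothing to its true sampling error. A model without area does not know this. It sees schools that differ and puts the whole area difference into the school variance.

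With 8 schools this matters, because school variance dominates: 0.04 of the 0.0496 sigma² variance of a school mean. At stake are confidence intervals wider than the design warrants, and power, for the primary comparison and for the workshop and coaching comparisons.

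The reliance on change scores under Study Design does not settle it. Change scores remove differences in level between schools, not a difference between areas in how much children change.

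**Working it through.** **Inputs (Sample Size and Randomization).** Effect 0.5 sigma; intraclass correlation of change 0.04; 100 children per school; 4 schools per arm; 5% level, taken as two-sided. The area difference in mean change, δ, is not given, so a range is used.

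**The plan's own figure.** Design effect 1 + 99 × 0.04 = 4.96. Effective children per arm 400 / 4.96 = 80.6. Standard error √(2 / 80.6) = 0.1575 sigma. Normal approximation: 0.5 / 0.1575 = 3.175; 3.175 − 1.960 = 1.215; power 88.8%. This agrees with the stated figure of over 85%. The same inputs with a t reference on 6 degrees of freedom give 75%.

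**Bias.** In the 8-school layout described above, the correlation of area with each of the three indicators is exactly 0. Leaving area out does not shift any of the three estimates.

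**Standard error.** Let s² be the variance of a school mean within an area. Without area, each of the 8 schools contributes an extra (δ/2)² to the residual sum of squares, 2δ² in all. The expected residual mean square becomes:
- 4-versus-4 model (6 df): s² + 2δ²/6 = s² + δ²/3
- three-indicator model (4 df): s² + 2δ²/4 = s² + δ²/2

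The true sampling variance still depends on s² alone. For δ = 0.3 sigma and s² = 0.0496, the 4-versus-4 mean square is 0.0496 + 0.0300 = 0.0796. The standard error implied by this is √(0.0796 / 2) = 0.20, against a true √(0.0496 / 2) = 0.1575.

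**Power and error, t reference.** Simulation of 8 school means, 400,000 replicates, equal school sizes, class-level variance ignored. Where area is a share f of the 0.04, δ = 2√(0.04f) and s² = 0.04(1 − f) + 0.0096. Each cell is without / with area. The last column is the intervention coefficient at 0.5 sigma; the workshop coefficient gives the same figures to within about a tenth of a point.

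| Area difference | δ (sigma) | s² | 4-vs-4 power | 4-vs-4 error | Three-indicator power |
|---|---|---|---|---|---|
| none | 0 | 0.0496 | 75% / 72% | 5.0% / 5.0% | 40% / 35% |
| quarter of the 0.04 | 0.20 | 0.0396 | 75% / 81% | 2.9% / 5.0% | 33% / 41% |
| half of the 0.04 | 0.28 | 0.0296 | 74% / 90% | 1.1% / 5.0% | 23% / 51% |
| on top of the 0.04 | 0.20 | 0.0496 | 67% / 72% | 3.2% / 5.0% | 29% / 35% |
| on top of the 0.04 | 0.30 | 0.0496 | 56% / 72% | 1.8% / 5.0% | 18% / 35% |

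**Break-even.** With the difference on top of the 0.04, 4-versus-4 power is 72.2% / 72.0% at δ = 0.12. Three-indicator power is 34.3% / 34.6% at δ = 0.14. Below roughly 0.12 to 0.14 sigma the lost degree of freedom outweighs the gain.

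**Error, normal reference.** For 4 versus 4 without area: 9.8% at δ = 0, 6.2% in the quarter case, 4.3% at 0.3 sigma on top. It falls below 5% only from about 0.27 sigma on top. With area it is 10.7% throughout. In the three-indicator model at δ = 0 it is 12.2% without area and 14.5% with it.

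**The case against.** **The covariate list is not closed.** The intervention models take the three indicators in addition to other terms, and the sentence before allows personal characteristics and other potential confounders. A fuller plan could add area. This stands in part: area is unmentioned, not excluded. But the confounder wording is tied to the cross-sectional models, and a factor balanced over the arms is not one that a confounder rule would pick. The article does count and name its school-level terms, and the stratification factor is not among them.

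**The size is unknown.** This stands. The document describes different communities, not different 36-week changes, and all 8 schools come from the same poverty quintile. A difference on top of the 0.04 also means more between-school variance than the protocol assumed.

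**The tests may not be conservative.** A reader might infer that leaving area out pushes the true error rate well below 5%. The document does not support that as a general statement. It needs a small-sample t reference, which the article never states, and the stated power reproduces with a normal approximation. Under a normal reference the test without area is already liberal for small or moderate area differences, and leaving area out partly offsets this.

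**The cost can be understated.** Three power points is the cost for the 4-versus-4 model only. In the three-indicator model that the article describes, it is about 6.

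**Area overlaps with an interaction.** Among the intervention schools, area coincides with the workshop-by-coaching interaction. This stands as a limitation, but the three-indicator model already assumes that interaction away, and the control schools also inform the area term.

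**Conclusion.** The point holds as a matter of efficiency, not validity. The listed school-level terms do not match the stratified randomisation. No effect estimate is biased. If the areas differ in change, standard errors are too large for the design and power is lost. With a t reference, the area term gains about 6 points for the 4-versus-4 comparison when a quarter of the assumed between-school variance is area, and about 16 when half is or when 0.3 sigma comes on top. If the areas do not differ, it loses about 3 points there and about 6 in the three-indicator model.

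The figures rest on the protocol's planning inputs, equal school sizes, no separate class variance, and an assumed area difference. A claim of error rates below 5% goes only as far as a t reference is used.

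**What to change.** Add one fixed indicator for the randomisation stratum (township versus northern) to the intervention-effect models, the 4-versus-4 comparison first. In the same sentence, state a small-sample correction with school-level residual degrees of freedom: 5 for the pooled comparison and 3 for the three-indicator model. The two belong together, since the indicator with a normal reference leaves error at about 11% and 14.5% respectively.

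The covariate is already known for every school, so the work is a sentence or two in the analysis section. The price is one school-level degree of freedom, with the power loss given above if the areas do not differ. The plan should also say that the area term assumes no workshop-by-coaching interaction.
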